#### 5.1.2.2 Analysis in PPS

The per protocol analysis will be conducted in PPS. The results will be presented in **Table 3**.

## 5.2 Secondary outcomes

Secondary outcome for the effectiveness of intervention includes DBP, 24h urinary sodium, 24h urinary potassium and microalbumin, EQ-5D and events.

### 5.2.1 Analysis for continuous secondary outcome

For continuous secondary outcomes we will use the same models as that for the primary outcome to test the difference between intervention groups.

If the distribution of the outcome variable is normal or mild skew, no transformation will be applied. If the outcome variable is heavily right-skewed, a log transformation will be conducted.

If the outcome variable is heavily left-skewed, a power transformation (e.g. box-cox transformation) will be conducted.

Results for continuous secondary outcomes will be reported in **Table 2** and **Table 3**.

### 5.2.2 Analysis for events

Frailty survival models (cox proportional hazards model with mixed effects) that account for within-cluster homogeneity will be used for the analysis of all-cause mortality, cardiovascular events (fatal and nonfatal stroke, fatal and nonfatal myocardial infarction, hospitalization or death caused by congestive heart failure). The proportional hazards assumption will be confirmed using statistics and graphs based on the Schoenfeld residuals. If more than one events took place during the study period, only the first event will be counted. Separated models will be built for each intervention, either SS alone or SSSC alone. The cluster(facility) will be regarded as the random effect. The models would be:

$$h_{ij}(t) = h_0(t)\exp(\beta_1 x_{ij} + \mu_j)$$

Where  $h_{ij}(t)$  is the hazard function for the  $i^{\text{th}}$  subject in  $j^{\text{th}}$  cluster.  $h_0(t)$  denotes the baseline hazard function. ;  $x_{ij}$ , the predictor of interest, either SS alone or SSSC alone, is an indicator of the intervention for subject  $i$  in cluster  $j$  (1 indicates receive intervention while 0 indicates not receive intervention);  $\beta_1$ , the coefficient of interest, is the effect coefficient of intervention;  $\mu_j$  denotes the random effect associated with the  $j^{\text{th}}$  cluster. An additional multivariate model will be conducted to controlling for the potential unbalanced covariates at baseline, if any.

The results for event will be presented in **Table 4** and **Table 5**.

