**Investigations on the elderly include:**

-Contents:

**Questionnaire: General Demographic Data:** Gender, age, ethnic group, education level, marital status, and medical insurance of the participant.

**Lifestyle Information:** Smoking, alcohol consumption, level of physical exercise, frequency of fruit and vegetable consumption.

**Level of Satisfaction in Meals:** How much they liked the meals provided by the nursing home, self-assessment of the level of saltiness in meals.

**Disease History:** Whether or not they are suffering from hypertension, diabetes, stroke, coronary heart disease, kidney disease, cancer, or COPD. As well as other disease histories and whether they are receiving treatment.

**Information on Antihypertensive Drugs:** Type, specification, and frequency of consumption of antihypertensive drugs.

**Occurrence of an Endpoint Event:** Whether or not there is all-cause mortality or cardiovascular events (coronary heart disease, congestive heart failure, heart arrhythmia, and stroke).

**Health Status:** Will be evaluated using the EuroQol Five Dimensions Questionnaire (EQ-5D).

**Physical Examination:** Weight, height, blood pressure, heart rate.

**Laboratory Examination:** Serum electrolytes (blood potassium), blood sugar and four items of blood lipid, kidney function (serum creatinine), and blood routine. Levels of 24-hr urinary sodium, urinary potassium, urinary creatinine, and quantitative microalbuminuria.

**Eye Fundus Examination:** Vision test and funduscopy.

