#### **5.1.1 Primary analysis**

The primary analysis will be performed in FAS dataset. The results will be regarded as the main findings.

A pre-specified linear mixed effects model will be performed to model repeated measures of SBP of the same individual over time. The model will include intervention status and baseline SBP as fixed effects, as well as cluster and time as random effects. Separated models will be built for each intervention, either SS alone or SSSC alone. The model would be:

$$y_{ijt} = \beta_0 + \mu_{1i} + \mu_{2j} + \beta_1 x_{ij} + \beta_2 c_{ij} + \beta_3 t + e_{ijt}$$

$$e_{ijt} \sim N(0, \sigma_e^2)$$

$$\mu_{1i} \sim N(0, \sigma_{\mu 1}^2)$$

$$\mu_{2j} \sim N(0, \sigma_{\mu 2}^2)$$

Where  $i$  represents the  $i^{\text{th}}$  subjects,  $j$  represents the  $j^{\text{th}}$  cluster (facility),  $t$  represents time point  $t$ ,  $y_{ijt}$  is the SBP measured for subject  $i$  in cluster  $j$  at time  $t$  (follow-up month), baseline SBP will not be included in  $y_{ijt}$ ;  $\beta_0$  is the mean outcome in the control group at baseline;  $\mu_{1i}$  is an individual random effect to allow for multiple repeats per person;  $\mu_{2j}$  is a cluster random effect on baseline SBP to allow for between-cluster heterogeneity;  $x_{ij}$ , the predictor of interest, either SS or SSSC, is an indicator of the intervention for subject  $i$  in cluster  $j$  (1 indicates receive intervention while 0 indicates not receive intervention);  $\beta_1$ , the coefficient of interest, is the effect coefficient of intervention;  $c_{ij}$  is the baseline SBP measured for subject  $i$  in cluster  $j$ ;  $e_{ijt}$  is the random error for the measurement of subject  $i$  in cluster  $j$  at time  $t$ .

The estimation of  $\beta_1$ , its 95% confidence interval and the corresponding  $p$  value will be reported in **Table 2**.

We will also evaluate the interaction between SS and SSSC in lowering SBP during study period. If the effect of both interventions do exist, we will add interaction term in the above model to test the interaction between SS and SSSC. The model would be:

$$y_{ijt} = \beta_0 + \mu_{1i} + \mu_{2j} + \beta_1 x_{1ij} + \beta_2 x_{2ij} + \beta_3 x_{1ij} * x_{2ij} + \beta_4 c_{ij} + \beta_5 t + e_{ijt}$$

$$e_{ijt} \sim N(0, \sigma_e^2)$$

$$\mu_{1i} \sim N(0, \sigma_{\mu 1}^2)$$

$$\mu_{2j} \sim N(0, \sigma_{\mu 2}^2)$$

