#### 5.1.2.1 Controlling for potential confounders

We will test if there is any imbalance between groups in baseline variables. We will additionally include the covariates that differs significantly at the baseline ( $p<0.05$ ) to adjust confounding.

The models would be:

$$y_{ijt} = \beta_0 + \mu_{1i} + \mu_{2j} + \beta_1 x_{ij} + \beta_2 c_{ij} + \sum BZ_{ij} + \beta_3 t + e_{ijt}$$

$$e_{ijt} \sim N(0, \sigma_e^2)$$

$$\mu_{1i} \sim N(0, \sigma_{\mu 1}^2)$$

$$\mu_{2j} \sim N(0, \sigma_{\mu 2}^2)$$

Where  $i$  represents the  $i^{\text{th}}$  subjects,  $j$  represents the  $j^{\text{th}}$  cluster (facility),  $t$  represents time point  $t$ ,  $y_{ijt}$  is the SBP measured for subject  $i$  in cluster  $j$  at time  $t$  (follow-up month), baseline SBP will not be included in  $y_{ijt}$ ;  $\beta_0$  is the mean outcome in the control group at baseline;  $\mu_{1i}$  is an individual random effect to allow for multiple repeats per person;  $\mu_{2j}$  is a cluster random effect on individual baseline SBP to allow for between-cluster heterogeneity;  $x_{ij}$ , the predictor of interest, either SS or SSSC, is an indicator of the intervention for subject  $i$  in cluster  $j$  (1 indicates receive intervention while 0 indicates not receive intervention);  $\beta_1$ , the coefficient of interest, is the effect coefficient of intervention;  $c_{ij}$  is the baseline SBP measured for subject  $i$  in cluster  $j$ ;  $Z_{ij}$  is the baseline covariate other than SBP measured for subject  $i$  in cluster  $j$ ;  $e_{ijt}$  is the random error for the measurement of subject  $i$  in cluster  $j$  at time  $t$ .

If the interaction effect in primary analysis exists, then below model will be built for adjustment of covariates:

$$y_{ijt} = \beta_0 + \mu_{1i} + \mu_{2j} + \beta_1 x_{1ij} + \beta_2 x_{2ij} + \beta_3 x_{1ij} * x_{2ij} + \beta_4 c_{ij} + \sum BZ_{ij} + \beta_5 t + e_{ijt}$$

$$e_{ijt} \sim N(0, \sigma_e^2)$$

$$\mu_{1i} \sim N(0, \sigma_{\mu 1}^2)$$

$$\mu_{2j} \sim N(0, \sigma_{\mu 2}^2)$$

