#### 5.6 Subgroup analysis

The following pre-specified subgroup analyses will be performed on the primary outcomes and safety outcomes stratified by:

- 1) baseline blood pressure:
  - a. normal: baseline SBP < 140mmHg and DBP < 90mmHg
  - b. stage 1: baseline BP 140-159/90-99mmHg
  - c. stage 2 or above: baseline SBP > 160mmHg or DBP > 100mmHg
- 2) hypertension status:
  - a. normotensive: baseline BP < 140/90mmHg and not taking antihypertensive medication within 2 weeks before baseline
  - b. hypertensive: had baseline SBP  $\geq$  140mm Hg or DBP  $\geq$  90mmHg, or on antihypertensive medications within 2 weeks before baseline
- 3) region:
  - a. Changzhi
  - b. Xi'an
  - c. Hohhot
  - d. Yangcheng
- 4) Sex:
  - a. Male
  - b. Female
- 5) Age
  - a. < 70 years
  - b.  $\geq$  70 years

Using 70 years as the cut-off is because the mean age at the baseline was about 71 years.
- 6) educational attainment
  - a. illiterate, semi-illiterate or completed primary school
  - b. completed junior high school or above

Results will be presented on forest plots in **Figure 3** with the interaction results alongside

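### The main model for death and cardiovascular events uses no baseline covariate, and no planned event analysis is certain to adjust for age; the model is valid but gives up precision

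*Supplement*

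**What the plan says.** SAP 5.2.2 states: "Frailty survival models (cox proportional hazards model with mixed effects) that account for within-cluster homogeneity will be used for the analysis of all-cause mortality", and likewise for cardiovascular events, with separate models for SS and SSSC. The model is h0(t)·exp(β1·x + μj), where x is the intervention indicator and μj a facility effect: "The cluster(facility) will be regarded as the random effect". Age, sex, disease history and region do not appear, although region stratified the randomisation (SAP 2.4).

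The section then adds: "An additional multivariate model will be conducted to controlling for the potential unbalanced covariates at baseline, if any". It names no covariate and gives no rule for finding imbalance. The rule in SAP 5.1.2.1, written for SBP, is: "We will additionally include the covariates that differs significantly at the baseline" at p<0.05. Results without covariates go to Table 4 and adjusted results to Table 5.

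Other parts of the plan bear on this:
- The SBP model always adjusts for one baseline value: "The model will include intervention status and baseline SBP as fixed effects, as well as cluster and time as random effects" (SAP 5.1.1).
- The secondary hyperkalaemia analysis lists its adjustment conditions in advance (SAP 5.3.2.1).
- Subgroup analyses, including those by age, cover only primary and safety outcomes (SAP 5.6).
- Protocol V1.4 section 5.2 collects "Gender, age, ethnic group, education level, marital status, and medical insurance of the participant" at baseline, along with disease history. Randomisation follows baseline collection (section 5.3).
- Protocol V1.4 section 9 counts cardiovascular event risk among the secondary outcomes and says the mixed model will control for clustering and confounders. The comparison it then spells out concerns blood pressure.

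**The concern.** Whether sodium reduction lowers cardiovascular events and death is a stated secondary aim (SAP 1.2). Age can be expected to predict both outcomes strongly in residents whose mean age is about 71. Each factorial comparison sets 24 facilities against 24, and homes may house residents of different ages. A facility frailty can turn such differences into a wider interval. It cannot remove an age gap that happens to fall between the two arms, and age differences within a facility go unused. At stake are the precision of the event hazard ratios and how they would be read if the arms turned out to differ in age.

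**Working it through.** The plan states no event number, hazard ratio or power for death or cardiovascular events. Its power figures concern SBP only, so there is no stated figure to reproduce.

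**Inputs from the documents.** 48 facilities allocated 1:1:1:1, hence 24 v 24 per comparison (SAP 2.4); 20 residents per facility (SAP 2.5); 24 months of follow-up (SAP 2.8); two-sided 5% tests (SAP 3.1); "the mean age at the baseline was about 71 years" (SAP 5.6). SAP 5.9 calls mortality high and gives no rate.

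**Assumed inputs.** Age SD within a facility sw = 7-8 years; SD of facility mean age sb = 1-4 years; log-hazard b = 0.07-0.09 per year of age (0.08 in the simulation); residual frailty SD 0.2; 2-year mortality 8%, 15% or 25%; true hazard ratio 0.65.

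**1. Chance age gap between the arms.** SD of the gap = √[2·(sb² + sw²/20)/24].
- sb = 1, sw = 7: √[2·(1 + 2.45)/24] = 0.54 years.
- sb = 2, sw = 8: √[2·(4 + 3.2)/24] = 0.77 years.
- sb = 4, sw = 8: √[2·(16 + 3.2)/24] = 1.26 years.

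A gap of one SD multiplies the unadjusted hazard ratio by about exp(b·SD). This runs from exp(0.07·0.54) = 1.04 to exp(0.09·1.26) = 1.12. A gap of 1.96 SD multiplies it by 1.08 to 1.25.

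**2. Validity of the unadjusted model.** Trials of 48 × 20 residents were simulated with exponential survival and normal facility frailty, and fitted by penalised likelihood with an exponential baseline hazard (500-800 runs per setting). With no true effect, the mean unadjusted hazard ratio was 0.99-1.00 and type I error 4.6-6.5%. There is no systematic bias. Across the null and HR 0.65 runs, the unadjusted log hazard ratio correlated 0.22-0.58 with the age gap.

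**3. Gain from adding age** (true hazard ratio 0.65; sw = 8 where sb = 2 and 7 where sb = 4). The variance ratio is the squared ratio of the two SDs, e.g. (0.157/0.180)² = 0.76.

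| 2-year mortality | sb (years) | Mean events | SD of log HR, without → with age | Variance ratio | Power, without → with age |
|---|---|---|---|---|---|
| 8% | 2 | 64 | 0.279 → 0.276 | 0.98 | 34.9% → 35.9% |
| 8% | 4 | 64 | 0.296 → 0.282 | 0.91 | 34.5% → 36.4% |
| 15% | 2 | 121 | 0.204 → 0.200 | 0.96 | 53.1% → 56.5% |
| 15% | 4 | 121 | 0.218 → 0.201 | 0.85 | 51.1% → 56.9% |
| 25% | 4 | 204 | 0.180 → 0.157 | 0.76 | 65.5% → 78.2% |

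Simulation noise is about 2 points on each power, so the gains at 8% mortality cannot be told from zero.

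**4. Would the adjusted model bring age in?** Suppose the p<0.05 rule of SAP 5.1.2.1 were used for events with a test that ignores clustering. With ICC = sb²/(sb² + sw²) and design effect D = 1 + 19·ICC, the chance that age is selected is 2·[1 − Φ(1.96/√D)].
- sb = 2, sw = 8: ICC = 4/68 = 0.059, D = 2.12, chance 18%.
- sb = 4, sw = 7: ICC = 16/65 = 0.246, D = 5.68, chance 41%.

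Over all assumed spreads the chance is about 9-41%, so age would more often than not be left out of Table 5.

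**The case against.** The strongest reply is that nothing is wrong. Facilities are randomised, the frailty accounts for clustering, and step 2 shows a valid test. The shift in step 1 is part of the sampling error that the interval already carries, not an extra harm. This stands. A reader might infer that age confounds the hazard ratios; the design and the null simulations do not support that.

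An adjusted model is also planned, and the SAP does not say which table leads. This stands in part: that model is called additional, applies only if imbalance is found, and names no covariate.

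The contrast with SBP is weak, since that model adjusts for the baseline value of the outcome and likewise omits age and sex. This stands; the case does not depend on it.

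The size is assumed. A reader might infer that events are few and the loss of power large. No event count is given, SAP 5.9 speaks of high mortality, and with few events the gain is only 1-2 points. A gain such as 34% to 53% can be produced, but it took an assumed facility age SD of 5 years, which no document supports, and a fit described without a frailty term.

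Two limits of the working also stand. Stratification by region was not simulated and would reduce age gaps if ages differ by region. Part of the power gain arises because the conditional hazard ratio lies further from 1 (mean 0.646-0.649 with age, 0.651-0.662 without), not only from a narrower interval.

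**Conclusion.** The point holds as a matter of precision and advance specification. The main event model uses no baseline covariate, and no planned event analysis is certain to use age. The hazard ratio is not biased, but it is less precise than it could be and open to chance differences in resident mix. Under the stated assumptions adding age gains about 1 to 13 points of power, the upper end needing 25% mortality and a facility mean-age SD of 4 years. A one-SD age gap shifts the unadjusted hazard ratio by about 4-12%. Neither range can be narrowed from the documents. The simulation used an exponential baseline hazard in place of the Cox model and added age only, so no gain is claimed for sex, disease history or region. The outcome is secondary and has no stated power; the change is worth making because it is cheap.

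**What to change.** In SAP 5.2.2, write the main event model as h0(t)·exp(β1·x + γ·Z + μj). Fix Z in advance as age (continuous), sex, baseline history of stroke or coronary heart disease, and region, the stratification factor. Report this model in Table 4 for both all-cause mortality and cardiovascular events, and keep the model without covariates as supportive. State how a missing history item is handled, so that residents are not dropped without notice.

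The cost is wording only, since these items are already planned for collection at baseline. The hazard ratio becomes conditional on the covariates, and six coefficients are added (one each for age, sex and history, three for four regions). If events prove few, the benefit will be small.

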### 5.3 Analysis for safety outcome

All analysis for safety outcomes will be conducted on safety dataset.

### 5.3.1 safety outcomes

The safety outcomes include:

- 1) Incidence of hyperkalemia;
- 2) Incidence of renal dysfunction;
- 3) Incidence of hyponatremia;
- 4) Mean serum potassium and sodium during follow-up

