## **7.3 Other Possible Trial-Related Adverse Reactions**

Gastrointestinal adverse reactions: Participants complain about symptoms such as nausea, vomiting, and diarrhoea. Should these reactions occur, the nursing home should be notified to send the participants to the hospital for treatment. Get a doctor to diagnose if the symptoms are a result from the intervention strategies. If these adverse reactions are due to the intervention strategies of this research, then the participants must be stopped for the research. The participants can discuss with the nursing home to be transferred to a nursing home that is not participating in the research. Alternatively, the cooks of the nursing home may prepare food using regular salt just for the participants.

Changes in blood pressure: The blood pressure of participants who regularly take antihypertensive drugs must be routinely monitored during the research period. If there is a significant decrease in their blood pressure, notify the nursing home and send them to the hospital. Get a doctor to gradually adjust the prescription of the drugs to prevent any fainting incidents that might result from an overly low blood pressure. After the research has ended, conduct a follow-up on the participants who regularly take antihypertensive drugs and monitor the changes in their blood pressure after the salt reduction strategies have ended. The prescription of their drugs should be adjusted to prevent any sudden increase in their blood pressure.

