## **7.4 Serious Adverse Events**

A serious adverse event (SAE) is defined as having any of the following outcomes resulting from the intervention:

- Threat to life
- Requiring hospitalization
- Permanent or significant disability and dysfunction

Should an SAE occur during the course of the research, researchers must adopt the suitable treatment measure on the participant immediately and end the trial.

Should an SAE occur, researchers have to find out the details and record the following content, whether or not it has to do with the intervention strategies: Time of occurrence, end time, measures adopted, relationship with the investigational drugs, etc. For expected SAEs that are unrelated to the research, researchers have to conduct the appropriate recordkeeping and report it to the Ethics Committee after the research is over. For unexpected SAEs or SAEs that are related to the research, a report has to be made in accordance with the provisions of the Ethics Committee.

Should any adverse events occur, researchers have to record the following on the CRF: Time of occurrence, level of severity, end time, measures adopted, and outcome.

The severity of adverse events can be classified into the following 3 levels:

- Mild: Light symptoms and physical signs. Usually a one-off event that does not require treatment and will not affect daily activities. Symptoms would automatically be relieved with rest;
- Moderate: Symptoms and physical signs persist for a longer time. Slightly affects daily activities. Will recover with simple treatment;
- Severe: Symptoms and physical signs persist for an even longer period. Severely affects normal work and activities. Will not easily recover with simple treatment.

Researchers must immediately tend to adverse events that occur during the process of the research appropriately and in accordance with medical guidelines. Researchers can increase the number of follow-ups and laboratory tests on the participants if necessary. Follow-ups should be conducted until the adverse event is resolved or until the participant is in stable condition or fully recovers.

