### **Safety Evaluation:** Use PP to analyze the results

Make use of a multilevel mixed-effects model to control the clustering effect and confounding variables. Compare the changes in blood potassium levels before and after the intervention, changes in the accumulated number of hyperkalemia incidences before and after the intervention, and incidences of other possible adverse reactions between SS and non-SS. Make use of a multilevel mixed-effects model to control the clustering effect and confounding variables. Compare the changes in blood potassium levels before and after the intervention, changes in the accumulated number of hyperkalemia incidences before and after the intervention, and incidences of other possible adverse reactions between SS + SSSC and SS only or SSSC only.

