**Table 6. Relative risk for safety outcomes**

| Total N                        |      | SS                    |         | SSSC |                       | p for interaction |
|--------------------------------|------|-----------------------|---------|------|-----------------------|-------------------|
| N(%)                           | N(%) | Relative risk (95%CI) | p value | N(%) | Relative risk (95%CI) |                   |
| Incidence of hyperkalemia      |      |                       |         |      |                       |                   |
| Incidence of renal dysfunction |      |                       |         |      |                       |                   |
| Incidence of hyponatremia      |      |                       |         |      |                       |                   |

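### The SAP does not carry over the protocol's between-arm comparison of other adverse reactions, and its list of changes from the protocol does not say so

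*Supplement*

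**What the plan says.** **Protocol V1.4.** Section 9 plans a multilevel mixed-effects comparison of "incidences of other possible adverse reactions between SS and non-SS" and of "incidences of other possible adverse reactions between SS + SSSC and SS only or SSSC only". It does so twice: under the adherence heading by ITT, and under Safety Evaluation by PP. Section 7.3 names two kinds of reaction. The first is gastrointestinal: "Participants complain about symptoms such as nausea, vomiting, and diarrhoea". The second concerns residents who regularly take antihypertensive drugs: "If there is a significant decrease in their blood pressure, notify the nursing home and send them to the hospital". Section 7.4 puts the events on record: "Should any adverse events occur, researchers have to record the following on the CRF". It also has SAEs recorded whatever their relation to the intervention.

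**SAP.** Section 1.2 sets a general safety aim, with hyperkalemia and hyponatremia singled out. Section 5.3.1 then lists incidence of hyperkalemia, of renal dysfunction and of hyponatremia, and finally "Mean serum potassium and sodium during follow-up". Section 5.3.2 gives models for these. Table 6, "Relative risk for safety outcomes", and its adjusted counterpart, Table 7, each have three rows: hyperkalemia, renal dysfunction and hyponatremia. Section 5.3.3 analyses extra potassium tests and a symptom and medication questionnaire at months 3 and 6, in the SS group only. Section 5.2.2 compares all-cause mortality and a defined set of cardiovascular events.

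**The concern.** Section 9 of the protocol commits to a randomised comparison of clinical reactions beyond hyperkalemia, and the SAP contains no outcome definition, analysis set, model or table row for it. An analyst working from the SAP would produce a safety report with no between-arm result for the two kinds of reaction that the protocol itself names. Section 7.3 has participants stopped when a gastrointestinal reaction is attributed to the intervention, so this is a harm that the trial acts on. If a comparison is added after the data have been seen, its definition, population and model will not have been pre-specified.

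**Working it through.** The point rests on comparing the two documents, and the plan states no figure on it to reproduce.

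**Step 1: is the protocol comparison implemented anywhere in the SAP?**
- Section 5.3.1: 4 of 4 outcomes are laboratory measures.
- Section 5.3.2: models are given only for those outcomes.
- Tables 6 and 7: 3 of 3 rows are laboratory-defined.
- Section 5.3.3: includes a non-laboratory measure (a positive questionnaire), but only SS recipients have it, so it has no comparator.
- Section 5.2.2 and Tables 4-5: all-cause death; fatal and nonfatal stroke; fatal and nonfatal myocardial infarction; hospitalization or death from heart failure. Neither gastrointestinal reactions nor falls in blood pressure are covered.
- Section 5.1 and Table 2: SBP and DBP are compared as means, where a reduction counts as benefit. Individual harmful falls are not counted.
- The follow-up schedule in 2.9 keeps an adverse event row, so the SAP expects the data. SAE is in the abbreviation list, but no analysis uses it.

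**Step 2: is the omission declared?** Section 5.9 lists the new primary outcome and model, the matching change to the continuous secondary outcomes, and the addition of renal dysfunction. It has no entry on other adverse reactions.

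**Step 3: how precise would the comparison be?** The documents give neither event risks nor an ICC for adverse reactions. The ICC of 0.02 in SAP 2.5 belongs to the SBP calculation. Risks of 2%, 5% and 10% and an ICC of 0.02 or 0.10 are therefore assumptions. Each margin has 480 residents, 20 per facility (protocol section 10).

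Design effect: DE = 1 + (20 − 1) × ICC, which is 1.38 at ICC 0.02 and 2.90 at ICC 0.10.

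95% half-width of the risk difference = 1.96 × √(2p(1 − p) × DE / 480).

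At p = 0.05:
- ICC 0.02: 1.96 × √(0.095 × 1.38 / 480) = 0.032
- ICC 0.10: 1.96 × √(0.095 × 2.90 / 480) = 0.047

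| Assumed risk | ICC 0.02 | ICC 0.10 |
|---|---|---|
| 2% | 2.1 points | 3.0 points |
| 5% | 3.2 points | 4.7 points |
| 10% | 4.5 points | 6.5 points |

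With 384 per margin (16 per facility, after the planned 20% loss) and ICC 0.02, DE = 1.30 and the half-widths are 2.3, 3.5 and 4.8 points. The blood-pressure outcome has a smaller denominator, because section 7.3 monitors only residents on regular antihypertensive drugs. Its interval would be wider than these.

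**The case against.** The SAP does not withdraw the protocol's comparison, and protocol section 9 still stands. SAP 5.3.1 does not say that its list is exhaustive, and SAP section 6 presents only the main tables. A reader might infer that these reactions are never to be compared between groups; the documents support only that the SAP leaves a planned comparison unimplemented. A reader might also infer that an arm comparison of SAEs was dropped. None was planned: section 9 speaks of other possible adverse reactions, and section 7.4 requires SAEs to be recorded and reported to the Ethics Committee. Nor is safety in the SAP wholly laboratory-based, since 5.3.3 analyses symptom reports, and under protocol 7.5 the monitoring board reviews safety data twice a year.

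The data also have limits. In the schedules of both documents, adverse events are collected as they arise, with no fixed visit. Gastrointestinal reactions depend on residents complaining. Purchasers and salt managers in SS facilities are trained on potential side effects (protocol 5.4, item 2.2), and SS residents have extra screening at months 3 and 6 (7.1). Reporting could therefore differ by arm without any difference in harm.

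All of this stands, and it limits how a result may be read. It does not supply the missing analysis: the questionnaire has no comparator, board review is not a reported comparison, and no section of the SAP defines or models the reactions.

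**Conclusion.** The point holds as a conflict between protocol V1.4 section 9 and SAP 5.3: a planned comparison of other adverse reactions has no counterpart in the SAP, and 5.9 does not declare this. Followed as written, the SAP compares no clinical events between arms other than all-cause death and the listed cardiovascular events. This conclusion rests on the text alone and not on any assumed risk or ICC.

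It would be tempting to add that the data are informative enough to settle the question. The documents do not support that. At an assumed 2% risk, the half-width (2.1 points at ICC 0.02) already exceeds the risk itself, and no ICC for these outcomes is given. The case for the comparison is that it was planned and concerns named harms, not that it will be precise. The change should be made before the analysis; the primary result does not depend on it.

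**What to change.** Reconcile the two documents as follows.

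1. **Outcomes.** Add to SAP 5.3.1 and Tables 6-7 the number and percentage of residents with a gastrointestinal adverse reaction, and of residents with a recorded fall in blood pressure that led to referral. Section 7.3 gives no threshold for a significant fall, so count the recorded referral. Use as denominator the residents on regular antihypertensive drugs at baseline, the group that 7.3 monitors.
2. **Contrasts.** Compare SS v non-SS and SSSC v non-SSSC with the facility mixed model in 5.3.2. Add either the protocol's contrasts of SS + SSSC with each single strategy or the interaction term that 5.3.2 already specifies.
3. **Population.** Analyse residents as randomised, in line with the ITT entry in protocol section 9, and do not require a baseline potassium. Declare in 5.9 that this departs from the safety set, which requires a baseline potassium and analyses by intervention received. State there how the duplicate ITT and PP entries in section 9 are resolved.
4. **Ascertainment.** Exclude events found only through the SS-only screening at months 3 and 6, and list them separately.
5. **Recommended addition, not planned in the protocol.** Tabulate by arm the residents with at least one SAE of any cause.

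The cost is SAP wording and a few table rows, using records that section 7.4 already requires. Precision will be low for rare events. Reports are spontaneous and SS facilities are trained on side effects, so arms may differ in reporting; the report should say so. If precision is quoted, give it over a range of ICCs. If the comparison is not wanted, 5.9 should record and justify its omission.
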